**Fig. 2 F0002:**
[figure not shown]
Intervention program. The participants belonging to the intervention group have seven group visits (group sessions on motivation; healthy dietary pattern and exercise; weight loss for those whose BMI was >28 kg/m^2^; and group sessions for all at 0, 1, 2, and 3 years for personal feedback from food records). Control groups have laboratory visits at 0 and 3 years, without any group sessions). FR, food record; FFQ, food frequency questionnaire; OGTT, an oral glucose tolerance test.

### Intervention

The 3-year lifestyle intervention includes group sessions and the use of a website designed for this study, which enables the distribution of material and virtual discussions between the participants and clinical nutritionists. Printed material and discussions by phone are provided for those who do not have access to internet. The first year of the intervention includes 4–6 meetings depending on participant’s BMI (Fig. 2).

At the beginning of the intervention, a group session is organized (group session 1, about 150 participants at a time), where the aims of the study and the importance of lifestyle changes to reduce the risk of T2D are presented (Fig. 2). Group sessions 2 and 3 deal with healthy diet and physical activity. Participants needing more advice and support related to weight loss (BMI > 28 kg/m^2^) have two additional group sessions (4 and 5). About 5–40 participants/group have participated in group sessions 2–5. The spouses of the participants are invited to the group sessions lasting about 90 min. Group sessions are also organized at 1 and 2 years (group sessions 6 and 7).

Throughout the study, the participants in the intervention groups are contacted monthly by the nutritionists *via* the website to ensure participants’ activity for the intervention. Those participants not having internet access are contacted by mail. The participants are encouraged to contact the clinical nutritionists anytime they have questions or concerns.

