Several diabetes prevention trials have been published on the effects of lifestyle changes (diet and physical activity), and a meta-analysis of these trials reported a 57% reduction in incident T2D (8). There are no previous trials investigating the effect of the genetic background of the participants (the number of the risk alleles for T2D) on the effect of the prevention of T2D. Therefore, the aim of the T2D-GENE trial is to investigate the effects of lifestyle intervention (diet, physical activity, and weight maintenance/weight loss) on the prevention of incident T2D and the worsening of hyperglycemia in people with a high number of T2D risk alleles compared with people with a low number of T2D risk alleles. The second aim of our study is to investigate whether a group-based intervention utilizing a website is as effective as is an individual-based intervention. The hypotheses of the study are that lifestyle intervention is efficient independent of the number of T2D risk alleles (high and low genetic risks of T2D), and that a group-based intervention is as effective as an individual-based intervention in the prevention of T2D.

The primary outcome of our study is incident T2D defined by fasting plasma glucose ≥7.0 mmol/l or 2-h glucose ≥11.1 mmol/l in an oral glucose tolerance test (OGTT) or HbA1c ≥ 47 mmol/mol (6.5%), according to the American Diabetes Association criteria (9), or drug treatment for T2D started during a 3-year intervention trial. The secondary outcomes are changes in glucose area under the curve (AUC) in an OGTT, changes in insulin secretion and insulin sensitivity, and incident cardiovascular disease (CVD) events (fatal or non-fatal myocardial infarction, fatal or non-fatal stroke, death from cardiovascular causes or incident heart failure).

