### Statistical analyses

The primary analyses for the outcomes (incident T2D) in the time-to-event analyses will be based on a Cox proportional-hazards model with the study group (intervention and control) as a covariate in the low and high GRS groups. Linear regression will be used to evaluate the effect of intervention on insulin sensitivity, insulin secretion, the glucose AUC, and other continuous variables. Comparison between the study groups at baseline and at the end of 3-year intervention will be carried out with t-test (continuous variables) intervention and chi-square test (non-continuous variables).

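### The intervention is delivered in session groups in one arm only, but the stated Cox and linear models make no allowance for session group, so standard errors will be too small if outcomes within groups are positively correlated

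*Protocol article*

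**What the plan says.** Group delivery is a defining feature of the treatment. One of the two study hypotheses in the introduction is that "a group-based intervention is as effective as an individual-based intervention".

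The Intervention section describes the format. The opening meeting is large ("group session 1, about 150 participants at a time"). Diet and physical activity are then covered in sessions 2 and 3. Sessions 4 and 5 give extra weight-loss support to those with BMI above 28 kg/m². For these four sessions, "About 5–40 participants/group have participated in group sessions 2–5". Further group sessions follow at 1 and 2 years, with no size given. Outside the sessions, "the participants in the intervention groups are contacted monthly by the nutritionists" through the website, or by mail for those without internet access.

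The legend of Fig. 2 gives the other arm: "Control groups have laboratory visits at 0 and 3 years, without any group sessions".

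The Statistical analyses section says that the primary time-to-event analysis will be "based on a Cox proportional-hazards model with the study group (intervention and control) as a covariate in the low and high GRS groups". For the continuous outcomes, "Linear regression will be used to evaluate the effect of intervention on insulin sensitivity, insulin secretion, the glucose AUC, and other continuous variables". It adds t-tests and chi-square tests for comparisons at baseline and at 3 years. It names no session-group term, robust variance or ICC. The sample size section applies no design effect.

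**The concern.** People taught in the same room share a session leader, the discussion and one another's company. They may also have been put together by time of recruitment or by BMI. Either route can make their outcomes more alike than those of two intervention participants taken at random. Because the control arm has no sessions, the data are partially nested, with clusters on one side of the comparison and individuals on the other.

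The Cox, linear, t-test and chi-square procedures, in the form in which they are described, take participants as independent. With positive correlation within session groups, they understate the variance in the intervention arm. What is at stake is chiefly the coverage of the confidence intervals for the intervention effect in each genetic risk score (GRS) stratum, and with it the error rate of the tests. Coverage is the firmer harm. If the intervention affected nobody, correlation created by shared delivery would vanish, and an inflated type I error would then need correlation that arose from how the groups were formed.

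**Working it through.** **Inputs from the protocol article**
- Session group size: about 5–40 (Intervention). The mean and the spread are not given.
- Clustering in the control arm: none (Fig. 2 legend).
- Arms of 300 and 300 within each GRS stratum, so equal arms (Abstract, Calculation of the sample size).
- Nominal alpha: 0.05 (Calculation of the sample size). Two-sided is assumed, since the article does not say.
- The Cox model is fitted in the low and high GRS groups (Statistical analyses).
- Participants and nutritionists are blinded to GRS (Participants).

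**Assumptions, not in the article**
- ICC of 0.01–0.05, with 0 and 0.001 as reference points.
- Session groups mix low and high GRS about equally. This is inferred from the blinding. A group of 5–40 then contributes about 2.5–20 members to each stratum.
- Equal group sizes, and equal outcome variance per person in both arms.

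The plan has no figure of its own on clustering to reproduce.

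**Formulas**
- Design effect in the intervention arm: DE = 1 + (m − 1) × ICC.
- Ratio of true to naive standard error of the arm difference: R = √((DE + 1)/2), because only one of two equal arms is inflated.
- True error of a nominal 5% test: 2 × (1 − Φ(1.96/R)).

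**Results within one GRS stratum (the analysis stated)**

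| Members per group in stratum (m) | ICC | DE | R | True error |
|---|---|---|---|---|
| any | 0 | 1 | 1 | 5.0% |
| 2.5 | 0.01 | 1 + 1.5 × 0.01 = 1.015 | √1.0075 = 1.004 | 5.1% |
| 2.5 | 0.05 | 1 + 1.5 × 0.05 = 1.075 | √1.0375 = 1.019 | 5.4% |
| 20 | 0.001 | 1 + 19 × 0.001 = 1.019 | √1.0095 = 1.005 | 5.1% |
| 20 | 0.01 | 1 + 19 × 0.01 = 1.19 | √1.095 = 1.046 | 6.1% |
| 20 | 0.05 | 1 + 19 × 0.05 = 1.95 | √1.475 = 1.214 | 10.7% |

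The naive standard error is 1/R of the true one. At m = 20 it is 4% too small at an ICC of 0.01 (1/1.046 = 0.956) and 18% too small at 0.05 (1/1.214 = 0.823). At m = 2.5 it is 0.4% and 2% too small.

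**Upper bound, not the stated analysis.** If both GRS strata were pooled and every group had the maximum of 40, DE would be 1.39 at an ICC of 0.01 and 2.95 at 0.05. R would be 1.093 and 1.405, and the true error 7.3% and 16.3%.

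**The case against.** **The article is silent; it does not assert independence.** The variance estimator is often left to an analysis plan, and a robust variance is compatible with the sentence on the Cox model. This stands in part: the point is a shortfall in the analysis as stated and not a contradiction. But the article does name its models and their covariate, and that choice does not fit the delivery that it describes. A better method is available at little cost.

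**The effect may be nil.** Only sessions 2 and 3 are small-group sessions described as for everyone. Sessions 4 and 5 depend on BMI, so group composition may have changed, and stability of membership is not reported. Much of the three years is website use, monthly contact and personal written feedback on food records. A few sessions need not produce a material ICC in 3-year diabetes incidence. This stands as a reason to expect a modest effect. It does not justify taking the ICC as zero.

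**Matching may work the other way.** Controls were matched on GRS, fasting glucose, age and BMI. Matching on prognostic factors, analysed without adjustment or pairing, tends to make naive standard errors too large. This stands: the net direction for this design is not established, and any offset is not quantified here.

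**A robust variance has its own weakness.** If groups were near 40, the 635 recruited participants would form only about 16 clusters (635/40 = 15.9). Sandwich variances are biased downward with so few. This stands, and the fix needs a small-sample correction.

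**Stronger readings to avoid.** A reader might infer that the standard errors are certainly too small, or that the type I error reaches 16.3%. The documents support neither. The first needs a positive ICC, which is not given. The second needs every group at the stated maximum, the highest assumed ICC, and pooling over GRS, whereas the Cox model is described within GRS groups. Nor are all these models primary: only the Cox analysis of incident diabetes is so described.

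**Conclusion.** The concern holds in conditional form. The design is partially nested and the stated models do not allow for it. If outcomes within session groups are positively correlated, the naive variance is wrong for the primary Cox model and for the linear models of the continuous outcomes.

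In the stated within-stratum analysis the likely size is small to moderate: a true error of about 5.1–6.1% at an ICC of 0.01 and 5.4–10.7% at 0.05, against the nominal 5%. These ranges rest on an assumed ICC, on groups that mix GRS strata, on equal group sizes, and on no offset from matching. With an ICC of 0 there is no effect. The change should be made because it is cheap and guards coverage whether or not correlation is present. The trial's conclusions are not shown to be at risk.

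**What to change.** - Record each intervention participant's session group. If it changed, use the group of session 2.
- Estimate the primary Cox model with a cluster-robust variance and a small-sample correction. The cluster is the session group in the intervention arm. Controls enter as singletons. If matching was individual, which the article does not say, use matched sets instead.
- For insulin sensitivity, insulin secretion, glucose AUC and other continuous outcomes, use a partially nested mixed model with a random session-group effect in the intervention arm only.
- Report the estimated ICC, which also bears on the trial's own question about group delivery.

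The cost is a few lines in the analysis plan, slightly wider confidence intervals, and retrieval of one variable, on the assumption that session attendance was recorded. No extra participants or visits are needed.

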### Diet

Dietary guidance in the intervention group is based on the Nordic (13) and Finnish nutrition recommendations, emphasizing appropriate energy intake, meal frequency, consumption of fruits, vegetables, and berries, quality of dietary fat, and carbohydrates, including sugar and fiber intakes (Table 1). Experience from the D2D project (14) has been utilized in the intervention as well. Overweight and obese participants are encouraged to lose weight. The minimum goal is not to gain weight during the intervention.

**Table 1 T0001:** Goals of nutrient composition of the intervention diet based on Nordic and Finnish nutrition recommendations

Nutrient	Goal
Vegetables, fruit, and berries (g/day)	≥500
Carbohydrate (E%, percent of energy intake)	45–60
Sucrose (E%)	<10
Fiber (g/day)	≥35
Fat (E%)	25–40
Saturated fat (E%)	<10
Monounsaturated and polyunsaturated fat (E%)	≥2/3 of total fat
Polyunsaturated fat (E%)	5–10
n-3 fatty acids (E%)	≥1
Monounsaturated fat (E%)	10–20

In addition to the quality and quantity of diet, aspects related to eating behavior are discussed in group sessions considering weight loss. The participants report their body weight weekly *via* the website or in writing (those who do not use internet). Dietary habits are evaluated by a food frequency questionnaire (FFQ) at baseline and at the end of the study. The FFQ is used previously in the FINRISK study (15), and with minor modifications and updates in the METSIM study (16). Four-day food records are used for measuring dietary intake enabling the evaluation of the achievement of the dietary goals. The intervention group keeps food records at baseline and at 6, 12, 24, and 36 months (Fig. 2). AivoDiet software (version 2.2.0.0, AivoFinland, Turku, Finland) is used for the calculation of dietary intake. Participants get personal written feedback on the food records based on the calculations to support their adherence to the dietary goals during the intervention.

### Physical activity

The goal regarding physical activity is brisk walking a minimum of 30 min per day at least 5 days a week. Walking could be replaced with other types of exercise (e.g. cycling, cross-country skiing, and housework such as leaves raking). Time used for physical exercise is recorded *via* website. Manual recording is possible for participants who do not have access to the internet.

### Laboratory analyses

Laboratory analyses are performed in the laboratory of Internal Medicine at the University of Eastern Finland. Insulin sensitivity is calculated as Matsuda index of insulin sensitivity and insulin secretion as Disposition index, as previously described (11).

### Statistical analyses

The primary analyses for the outcomes (incident T2D) in the time-to-event analyses will be based on a Cox proportional-hazards model with the study group (intervention and control) as a covariate in the low and high GRS groups. Linear regression will be used to evaluate the effect of intervention on insulin sensitivity, insulin secretion, the glucose AUC, and other continuous variables. Comparison between the study groups at baseline and at the end of 3-year intervention will be carried out with t-test (continuous variables) intervention and chi-square test (non-continuous variables).

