### Calculation of the sample size

The average proportion of participants in whom IGT progressed to T2D in the Finnish DPS study was 3%/year in the intervention group and 6%/year in the control group (4). The absolute incidence of T2D was 32 cases/1,000 person-years in the intervention group and 78/1,000 person-years in the control group (4). Using the results from the Finnish DPS study and assuming similar rates of incident T2D (6%/year) in the control group, a total of 69 individuals of 300 (our sample size) or 23% will develop diabetes during a 3-year intervention. The corresponding numbers in the intervention groups are 31 of 300 or 10%, indicating a 13% difference in incident T2D between these two groups. If α = 0.05 and β = 0.95, only 60 individuals/group are needed to demonstrate statistically significant difference between the intervention and control groups. Our group-based intervention might be less efficient than individual-based approach in the Finnish DPS study. If the effect of intervention is 6% (about half of the effect of that of the Finnish DPS study), then 267 participants are needed. Assuming around 10% of dropouts in this trial, a sample size of 300/each group has a power of 95% to demonstrate statistically significant reduction in incident T2D in the intervention groups compared with the control groups.

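### The single 95% power figure is not tied to a claim: the hypothesis needs the intervention to work in both genetic-risk groups, and at the planned 6-point effect the power for that is about 20%

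*Protocol article*

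**What the plan says.** All references are to the Protocol article.

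- **Hypothesis** (introduction, the text after the ClinicalTrials.gov ID): "The hypotheses of the study are that lifestyle intervention is efficient independent of the number of T2D risk alleles (high and low genetic risks of" … That is, the programme is expected to work at high and at low genetic risk.
- **Primary analysis** (Statistical analyses): the analysis of incident T2D "will be based on a Cox proportional-hazards model with the study group (intervention and control) as a covariate in the low and high GRS groups". The natural reading is one intervention-versus-control comparison in each stratum. This fits the design, in which each intervention group of 300 has its own matched control group of 300.
- **Power** (Calculation of the sample size): the full effect is taken as 23% in controls against "31 of 300 or 10%, indicating a 13% difference in incident T2D between these two groups". For that effect, "If α = 0.05 and β = 0.95, only 60 individuals/group are needed". A weaker effect of 6 points is then allowed for, said to need 267 participants. After about 10% dropout, "a sample size of 300/each group has a power of 95% to demonstrate statistically significant reduction in incident T2D in the intervention groups compared with" … (controls).
- **Interpretation** (Discussion): effects that do not depend on genetic risk would support the programme for everyone at risk; effects that do depend on it would call for tailored programmes.

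**The concern.** The power sentence speaks of intervention groups and control groups in the plural. It could mean either stratum, both strata, or all participants pooled. These claims have different power, and the article's hypothesis corresponds to the most demanding of them: both comparisons must succeed.

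Two things are at stake. First, a reader will take 95% as the chance of confirming the hypothesis, and a figure for one 300 versus 300 comparison cannot be that. Second, if power per stratum is moderate, one significant and one non-significant stratum becomes a common result even when the true effect is identical in both. Because the Discussion attaches opposite conclusions to independent and dependent effects, a chance split could be read as evidence that genetic risk matters.

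**Working it through.** **Inputs from the document.** Alpha 0.05; intended power 95% (printed once as β = 0.95); 300 per group, with 10% dropout leaving 270; control 3-year incidence 23% (69/300); full effect 23% versus 10%; reduced effect 6 points; two strata made up of different men.

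**Assumptions.** Two-sided tests (sidedness is not stated). The 6-point effect is 23% versus 17% (the base rate for it is not stated; others are tried below). The true effect is the same in both strata. Three-year proportions stand in for the Cox test, and the matching is ignored.

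**1. The article's own figures.** With n = [1.96·√(2p̄q̄) + 1.645·√(p₁q₁ + p₂q₂)]² / δ² for 95% power:
- 23% versus 10%: (1.029 + 0.850)² / 0.0169 = 209 per group, where the article has 60.
- 23% versus 17%: (1.109 + 0.928)² / 0.0036 = 1153 per group, where the article has 267.
- The dropout step agrees: 267/0.9 = 297, about 300.

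The printed 60 and 267 were not reproduced at 95% power by any variant tried. That is a separate matter from which claim the power covers, so step 2 takes the 95% at face value.

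**2. If 95% were true in each stratum.** The strata share no participants, so the two tests are independent.
- Both significant: 0.95² = 0.9025.
- Exactly one significant: 2 × 0.95 × 0.05 = 0.095.
- For 95% power for both, each stratum would need √0.95 = 97.5%.

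**3. Power at 23% versus 17%, 300 per group.** Power = Φ[(δ − 1.96·SE₀)/SE₁].
- SE₀ = √(2 × 0.20 × 0.80/300) = 0.03266; SE₁ = √((0.23 × 0.77 + 0.17 × 0.83)/300) = 0.03257.
- (0.06 − 0.06401)/0.03257 = −0.123, so power per stratum is 45.1%.
- Both: 0.451² = 20.3%. Exactly one: 2 × 0.451 × 0.549 = 49.5%. Neither: 0.549² = 30.1%.
- Pooled over the strata, 600 versus 600: (0.06 − 1.96 × 0.02309)/0.02303 = 0.640, so 73.9%.

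**4. Check of the proxy.** HR = ln 0.83/ln 0.77 = 0.713. Expected events are 300 × (0.23 + 0.17) = 120. Then (√120/2) × 0.338 − 1.96 = −0.106, giving about 46% per stratum, in line with step 3.

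**5. Sensitivity.**

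| Scenario | Per stratum | Both | Exactly one |
|---|---|---|---|
| 23% vs 17%, 300/group | 45% | 20% | 50% |
| 23% vs 17%, 270/group | 41% | 17% | 49% |
| 18% vs 12%, 300/group | 54% | 29% | 50% |
| 16% vs 10%, 300/group | 59% | 35% | 48% |
| 12% vs 6%, 300/group | 73% | 53% | 40% |
| 23% vs 10%, 300/group | 99% | 98% | 2% |
| 23% vs 10%, 270/group | 98% | 97% | 3% |

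The pooled test at 23% versus 17% with 270 per group has 69% power.

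**The case against.** **Splits come from low power, which is a different defect.** This is partly right. If the full 13-point effect holds, power for both strata is 97–98% and splits are rare. At a true 95% per stratum they occur 9.5% of the time. But the 300 per group and its 95% are derived for the 6-point effect, and the Discussion itself calls an insufficiently effective group-based programme the main challenge. Whatever the per-stratum figure, one number cannot serve as both the per-stratum power and the power of the two-stratum hypothesis.

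**Decision rules and alpha allocation may sit in an analysis plan not shown.** This stands, and their absence is not the point here. The power sentence and the hypothesis are printed in the article and do not correspond. The statistical paragraph is short, gives no alpha, and does not literally exclude one model covering both strata; that reading would still leave open which claim the 95% describes.

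**Readings the documents do not support.** A reader might infer that two tests at 0.05 give a 9.75% chance of falsely declaring the programme effective. The figure 1 − 0.95² = 9.75% counts a false result in either direction. A false result in favour of the intervention in at least one stratum has probability 1 − 0.975² = 4.9% with two-sided tests. Even this matters only if success in either stratum counts as trial success, and the article adopts no such rule. If both must succeed, the error rate is at most 5% without adjustment. A reader might also infer that a pooled test must come first as a gate. That is a trade-off, not a correction: if only one stratum benefits (23% versus 10% there, no effect in the other), gating lowers the power to detect it from about 99% to 81%, and the Discussion treats dependence on genetic risk as a key outcome.

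**Conclusion.** The concern holds for the power statement and for the reading of split results. It does not hold as a claim of inflated type I error. At the planned 6-point effect, read as 23% versus 17%, 95% is not the power of any of the three possible claims: about 45% per stratum, 20% for both and 74% pooled (41%, 17% and 69% with 270 per group). Lower base rates improve this to 54–73% per stratum and 29–53% for both at 300 per group, still well below 95%. About half of trials would split by chance at 23% versus 17%, and 40–50% across the base rates tried.

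These figures rest on two-sided 0.05 tests, an equal true effect in both strata, independent strata, and 3-year proportions as a proxy for the Cox model. The conclusion that one 95% cannot describe both a single stratum and both strata needs only the independence of the strata.

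**What to change.** 1. **Statistical analyses.** State that a claim of efficacy in both genetic-risk groups requires the intervention-versus-control comparison to be significant in each stratum, and that no alpha adjustment is needed for this claim. State that significance in only one stratum does not show that the effect depends on genetic risk.
2. **Calculation of the sample size.** Say which claim the power figure refers to, and restate it per stratum and for both strata, giving the base rate used for the 6-point effect and the sidedness of the test.
3. **Optional.** Report a pooled estimate stratified by GRS group as an addition. Using it as a gate for the stratum tests is not part of this fix.

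**Cost.** A few sentences and a short recalculation; no new data. The Time table section says recruitment closed in April 2018, so the restated power will not change the trial's size. Its use is in interpreting a non-significant or split result. The cost to the sponsor is that the restated figure for both strata will be much lower than the printed 95% unless the full 13-point effect is assumed.

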**Fig. 1 F0001:**
[figure not shown]
Study design of the T2D-GENE trial. Participants in the intervention and control groups of the trial are divided into two groups based on the genetic risk score for type 2 diabetes (low genetic risk and high genetic risk). IFG, impaired fasting glucose; IGT, impaired glucose tolerance. The duration of the intervention is follow-up time is 3 years for all participants.

For both intervention groups (low GRS and high GRS), control groups of 300 participants (altogether 600 participants) of the METSIM study were selected and matched for GRS, fasting plasma glucose concentration, age, and BMI (Fig. 1). The rationale for these two control groups is to compare the incidence of T2D during the intervention between the two intervention groups and the two control groups.

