### Time table

The first participants started the intervention in April 2016, and the recruitment was completed in April 2018. Altogether 635 participants were recruited. The first participants finished the 3-year intervention in April 2019, and the last participants will finish it in September 2021. The last participants in the control group will have a 3-year visit in September 2021.

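### Controls are matched on GRS, fasting glucose, age and BMI, but the named analyses do not use those variables, so a modest precision gain is left uncollected (minor)

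*Protocol article*

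**What the plan says.** **Design.** The Participants section (text under Fig. 1) describes "control groups of 300 participants (altogether 600 participants) of the METSIM study", which "were selected and matched for GRS, fasting plasma glucose concentration, age, and BMI". It gives no matching ratio or caliper, and does not say whether each control is tied to one intervention participant. The Time table section reports "Altogether 635 participants were recruited", and Table 2 gives n = 635 for the intervention group.

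**Analysis.** The Statistical analyses section bases the primary analysis on a "Cox proportional-hazards model with the study group (intervention and control) as a covariate in the low and high GRS groups". For continuous outcomes, "Linear regression will be used to evaluate the effect of intervention on insulin sensitivity, insulin secretion, the glucose AUC" and other variables; covariates are not listed. Study groups are also compared at baseline and at year 3 by "t-test (continuous variables) intervention and chi-square test (non-continuous variables"). No matching variable, matched-set term or robust variance is named. Fitting within low and high GRS respects part of the GRS matching.

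**Sample size.** The calculation makes no use of the matching.

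**The concern.** Fasting glucose is one of the components that define the primary outcome, and age and BMI are plausible predictors of it. When two groups are made alike on predictors of the outcome, the intervention-control contrast varies less from sample to sample than it would between two unrelated samples. An analysis that ignores those predictors still uses the larger, independent-sample variance. Its confidence intervals are then somewhat too wide and its tests somewhat conservative.

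What is at stake is efficiency, not validity. It matters most at the 6-point effect that sets the sample size, where power is lowest and where a null result in one GRS stratum could be misread as absence of benefit. Recruitment closed in April 2018, so the analysis is one of the few places where precision can still be gained.

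**Working it through.** **Inputs from the Protocol article** (Calculation of the sample size): control 3-year proportion 69/300 = 23%; intervention 31/300, about 10%; reduced effect of 6 points, read as 23% against 17%; 267 participants, read as per group; α = 0.05, taken as two-sided.

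**Assumed:** the within-pair correlation ρ of the binary outcome, which the article does not give. A simulated logistic risk score shared within pairs (overall risk 20%) gives ρ of 0.04, 0.09, 0.13 and 0.20 at c-statistics of 0.64, 0.71, 0.75 and 0.80. The range used is therefore 0.04 to 0.20.

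**Step 1. The plan's own figure.** The article claims 95% power from 267 per group, raised to 300 for dropout. With independent groups:
- Var_ind = [0.23×0.77 + 0.17×0.83]/267 = 0.3182/267, so SE = 0.0345.
- Power = 1 − Φ(1.96 − 0.06/0.0345) = 1 − Φ(0.22) = 41%.

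The 95% does not reproduce. Matching does not explain the gap: a McNemar calculation at ρ of 0.05 to 0.30 still needs about 1,100 down to 810 pairs. That is a separate and larger problem. Here, 41% is the base against which the gain is measured.

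**Step 2. Variance under matching.**
- Var_matched = Var_ind − 2ρ√(p1q1p2q2)/n, with √(p1q1p2q2) = 0.1581.
- Power of the matched test = 1 − Φ(1.96 − d/√Var_matched).
- Power of the independent-sample test = 1 − Φ((1.96√Var_ind − d)/√Var_matched).
- True size of the independent-sample test ≈ 2[1 − Φ(1.96/√(1−ρ))].

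| ρ (assumed) | SE too wide by | True size | Independent test | Matched test | Gain |
|---|---|---|---|---|---|
| 0.04 | 2.1% | 4.5% | 41% | 43% | 1.6 points |
| 0.05 | 2.6% | 4.4% | 41% | 43% | 2.0 points |
| 0.10 | 5.4% | 3.9% | 41% | 45% | 4.1 points |
| 0.15 | 8.4% | 3.4% | 40% | 47% | 6.5 points |
| 0.20 | 11.7% | 2.8% | 40% | 49% | 9.1 points |

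For 23% against 10% with 267 per group, both tests have 98% power or more throughout, and the gain is below half a point.

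**Step 3. The Cox model.** Simulation of 270 pairs, 4,000 runs, 23% against 17%, at outcome correlations of about 0.05 / 0.12 / 0.18:
- ordinary Cox: 41% / 40% / 40%;
- pair-robust variance: 43% / 46% / 49%;
- Cox stratified by pair: 38% / 40% / 43%.

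The pair-stratified form recovers little, and at low correlation it does worse than ignoring the pairs.

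**Step 4. Group-level matching, no pairs.** Simulation of controls frequency-matched to quintiles of a risk score, 267 per group, 8,000 runs, logistic model, score SD 0.5 / 0.8 / 1.0 / 1.3 (assumed):
- size, unadjusted: 4.8% / 4.3% / 3.5% / 3.0%; adjusted: 5.0% / 5.0% / 4.9% / 4.6%;
- power, unadjusted: 43% / 40% / 39% / 40%; adjusted: 44% / 44% / 44% / 49%.

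The gain is 1 to 9 points, so it does not depend on pairs existing.

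**The case against.** **Individual pairing is not documented.** A reader might infer that every intervention participant has his own matched control, so that a paired analysis is required. The wording fits group matching equally well, and 635 intervention participants against 600 planned controls rules out complete 1:1 pairs. This stands. The ρ figures therefore apply directly only if sets exist. The group-matching simulation keeps the point alive without them and makes covariate adjustment the main remedy.

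**Silence is not a decision.** Naming study group as a covariate does not say that the model is otherwise unadjusted, and a journal article may leave further covariates or variance estimators to a fuller document. This limits the point. What remains is that the article does name its model and tests, that t and chi-square tests as ordinarily understood are independent-sample procedures, and that following the text as written forgoes a gain available at almost no cost.

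**The t-test is not the main analysis of continuous outcomes.** That role belongs to linear regression with unlisted covariates. This stands, and no figure is claimed here for continuous outcomes.

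**The net direction is not established.** Group sessions act the other way. The Intervention section gives about 5 to 40 participants in sessions 2 to 5. With an assumed 20 per session and an assumed intraclass correlation of 0.01, intervention-arm variance rises by 19 × 0.01 = 19%. That arm supplies 0.1411/0.3182 = 44% of the contrast variance, so the contrast variance rises by about 8%. This is comparable with the 5% to 10% reduction from matching at ρ of 0.05 to 0.10. The conservatism described here is therefore the effect of ignoring the matching taken alone.

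**Conclusion.** The point holds as a minor one. The design matches on four variables, and the analyses as named use none of them beyond the low/high GRS split. Taken alone, this makes standard errors about 2% to 12% too wide in the paired calculation and forgoes about 1 to 9 power points at 23% against 17%. It is negligible at 23% against 10%. These figures rest on assumed correlations of 0.04 to 0.20 or the equivalent predictive strength. The upper end needs near-perfect matching and strong predictors in a sample already narrowed by eligibility (fasting glucose SD 0.3 mmol/l in Table 2).

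Two stronger readings are not supported. A reader might infer that the trial loses power: the unadjusted analysis has 39% to 43% power across these calculations, close to the 41% of an independent-groups plan, and the sample size counted on no gain from matching. A reader might also infer that the analysis is invalid: the error is conservative, and it does not raise type I error.

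**What to change.** In the Statistical analyses section:

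1. Within each GRS stratum, add baseline fasting glucose, age, BMI and risk-allele count as covariates to the Cox model and to the linear regressions.
2. Base the year-3 between-group effect estimates on those adjusted models rather than on unadjusted t and chi-square tests.
3. State whether matching was individual or by group. If identifiable matched sets exist, also use a robust variance clustered on the set, not a Cox model stratified by pair. The robust form keeps intervention participants who have no matched control.

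The cost is a sentence or two, plus a matched-set identifier in the dataset if sets exist. The covariates are the variables on which controls were selected, so no participants, visits or measurements are added. One small downside is that the hazard ratio becomes conditional on the covariates, which the report should say.
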